### Data Analyses

#### Sample Size and Power Analyses for the Quantitative Side of the Project

The sample size for this pilot study is constrained by financial and human resources. We plan to recruit a total of 21 participants, with 7 participants in each subjective socioeconomic group (refer to the *Participants* section). However, in terms of statistical power, we will benefit from the intensive longitudinal nature of the study, that is, 15 evaluation weeks and up to 105 daily observations per participant. For objective 1.1.a, for which a weekly environmentally sustainable healthy diet index will be used, up to 315 observations will be available in total (21 participants × 15 evaluation weeks) and 105 observations per socioeconomic group (7 participants × 15 evaluation weeks). For objective 1.1.b, for which the daily raw data will be used, up to 2205 observations will be available in total (21 participants × 105 daily assessments), 735 observations in the 3 socioeconomic groups (7 participants × 105 daily assessments), and 105 observations at the individual level (as a general rule of thumb, a minimum of 70 observations are required for conducting individual-level analyses [48]). Given the pilot nature of this trial, we conducted power simulation analyses only for objective 1.1.a (ie, change in the weekly level of food healthiness and environmental sustainability). Considering group-level analyses and the analytical strategy detailed in the next section and assuming an increase of 2 units in the environmentally sustainable healthy diet score per phase, simulated power analysis indicated an adequate power value of 96%. The simulation was performed by generating the response variable as follows:

Fixed effects: the intercept was set at 6, and the fixed coefficient for the phase was set as −2 for the initial phase and +2 for the final phase based on our average expected change in the main outcome.Random effects: it was assumed that each participant would have both a random slope and a random intercept and that both followed normal distributions, with SDs of 2 for the intercept and 0.5 for the slope. The correlation between them was set as 0.2. The random effect for each participant was created by drawing random numbers from a multivariate normal distribution whose covariance matrix was specified using these parameters (R mvrnorm from the package *MASS*).

Then, a linear mixed regression was performed on the data (R lme from the package *nlme*) using phase as a fixed effect and specifying a random slope and intercept for each participant across time. This process was repeated 1000 times, and the significance level for the fixed effect was 0.05.

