## Discussion

### Principal Findings

With regard to objective 1.1.a, we expect environmentally sustainable healthy diet to positively change over time (increasing score for the environmentally sustainable healthy diet index) with small to medium effect sizes, as observed in most previous behavior change interventions [14]. With regard to objective 1.1.b, which focuses on food groups and food waste and reflects the changes in the index, we expect the consumption of meat, dairy products, and ultraprocessed food to decrease over time and the consumption of unprocessed or minimally processed plant-based foods to increase. However, the rate of change might differ from one food group to another; for example, an increase in fruit and vegetable consumption might occur earlier in the intervention than a decrease in meat consumption, which might indicate that this second behavior is more difficult to change. At the individual level, we also expect the shape of those changes to be heterogeneous across participants, with linear improvements, 1-step changes, and inverse U–shape, for example. Objective 1.2 (feasibility of the study) is not hypothesis driven.

With regard to objective 2.1, we expect substantial mediation effects of motivations, ecoanxiety, habit, and self-efficacy on eating behaviors, with positive changes in eating behaviors being partially explained by positive changes in these variables. More specific hypotheses can also be formulated; for example, we expect motivation for protecting the environment to mediate changes in the food groups with the highest environmental impact (eg, meat) more than those in the food groups mainly relevant for health (eg, ultraprocessed food).

We do not have clear and specific hypotheses regarding the covariations among food groups and among dietary outcomes (objective 2.2) and hypotheses regarding the moderating role of participants’ socioeconomic level (objective 2.3), given that only a few studies have examined these dimensions before; overall, the participants from the lowest socioeconomic group may present a less healthy and environmentally sustainable diet than the participants belonging to the higher socioeconomic groups [27,58].

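### The 96% power for the diet index rests on a gain of 2 points per phase, continuing into follow-up, while the Discussion expects only small to medium effects on the same index

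*Protocol article*

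**What the plan says.** The sample-size section of the protocol article (Sample Size and Power Analyses for the Quantitative Side of the Project) gives one power figure, for objective 1.1.a. It reports an "increase of 2 units in the environmentally sustainable healthy diet score per phase, simulated power analysis indicated an adequate power value of 96" per cent. The simulation used an intercept of 6, and "the fixed coefficient for the phase was set as −2 for the initial phase and +2 for the final phase". These values were chosen "based on our average expected change in the main outcome". Random effects were normal, "with SDs of 2 for the intercept and 0.5 for the slope", with an intercept–slope correlation of 0.2. A linear mixed model with phase as fixed effect was fitted 1000 times at the 0.05 level.

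The Discussion (Principal Findings), writing about the same objective and index, expects a positive change "with small to medium effect sizes, as observed in most previous behavior change interventions".

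The Intervention section rules out feedback sessions in follow-up, and the caption of Multimedia Appendix 3 ties the text messages to the intervention phase. Under Qualitative Measurements, the final interview looks at whether acquired behaviors persist.

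**The concern.** The article gives two accounts of the expected effect on one outcome. The power section assumes a gain of 2 points at each phase, 4 points in all, on a 0 to 10 index. The Discussion expects something small to medium. Half of the assumed gain also arises after the active components have ended, whereas the rest of the article treats follow-up as a test of persistence.

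Effectiveness is a primary objective and this is its only power statement. If the true change is nearer to what the Discussion describes, readers may set a non-significant result against a quoted 96% and take it as evidence that the intervention does not work. A later full trial planned from this pilot could inherit that reading.

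**Working it through.** **Inputs from the protocol article.** 21 participants and 15 evaluation weeks; phase means 6 − 2 = 4, 6 and 6 + 2 = 8; intercept SD 2, slope SD 0.5, correlation 0.2; alpha 0.05; power 96%; index range 0 to 10.

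**Assumptions.** Two-sided test; weeks split 2 + 7 + 6 across the phases; small and medium taken as 0.2 and 0.5 SD. The article prints neither these benchmarks nor the residual SD.

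**Step 1: can the 96% be reproduced?** Not from the printed inputs alone. With the random slope on phase, the standard error (SE) of the intervention-minus-baseline contrast is √{[0.5² + s²(1/2 + 1/7)]/21}, where s is the residual SD.
- s = 1: √(0.893/21) = 0.206, and power at 2 points is about 100%.
- s = 2: √(2.821/21) = 0.367, and power is again about 100%.
- s = 3.02: √(6.113/21) = 0.54, and power is 96%.

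With the slope on week number or on rescaled time, 96% needs s of about 2.6 or 3.1. If the 96% belongs to the 4-point contrast or to a linear phase term, s must be about 3.6 to 6.5. Values above 5 are impossible on a 0 to 10 score, whose SD cannot exceed half its range.

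**Step 2: precision implied by the 96% for a 2-point contrast.** SE = 2/(1.960 + 1.751) = 2/3.711 = 0.539. The smallest change with 80% power is (1.960 + 0.842) × 0.539 = 1.5 points.

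**Step 3: power at smaller effects.** Power = Φ(δ/SE − 1.96); the opposite tail adds 0.3 percentage points at 0.4 point.

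| Scaling of the effect | Small (0.2 SD) | Medium (0.5 SD) |
|---|---|---|
| Intercept SD 2, SE 0.539 | 0.4 point: 11% | 1.0 point: 46% |
| Implied total SD 3.3–3.7, SE 0.539 | about 0.66–0.73 point: 23–27% | about 1.65–1.85 points: 86–93% |
| Intercept SD 2, residual SD 1 (SE 0.18–0.22) | 0.4 point: 43–61% | 1.0 point: 99% or more |

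The total SD is √(2² + 0.5² + s²): 3.29 for s = 2.57 and 3.70 for s = 3.07. The last row does not reproduce the plan's figure, because power at 2 points is then about 100%. If the 96% refers to the 4-point contrast, SE = 4/3.711 = 1.08, and changes of 0.4 and 1.0 point in that contrast have about 6% and 15% power.

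**Step 4: size of the assumed change.** Against the between-participant SD, 2/2 = 1.0 SD per phase. Against the total SD implied by a 2-point contrast, it is about 0.55 to 0.61 SD. Neither is small.

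**Step 5: gain only maintained in follow-up.** The means become 4, 6 and 6, so a linear phase term falls to half. If that was the term tested, δ/SE = 3.711/2 = 1.856 and power is Φ(1.856 − 1.96) = 46%. If the test was intervention against baseline, the follow-up assumption does not affect the 96%.

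**The case against.** A reader might infer that the study has 11% to 46% power for the effect it expects, or that the simulated effect is 1 SD per phase and 2 SD in total, two to five times too large. The documents do not support these as facts. The SD of 2 is the random-intercept component, not the SD of the outcome. Scaling the effect by 2 while taking an SE that implies a residual SD near 3 mixes two noise levels. On the matching total SD, 2 points per phase is close to a medium effect, and power at 0.5 SD is 86–93%. The Discussion also puts no number on small to medium and rests it on a cited source that is not at hand. This part of the objection stands.

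It is also fair that the sample was fixed by resources in a declared pilot, not derived from the 96%, and that no printed calculation is shown to be wrong. So the concern is with the power statement and not with the number of participants.

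The contradiction survives. No reading that yields 96% makes the simulated change a small effect, and small effects lie inside the range the Discussion expects. The further gain in follow-up has no stated basis and sits poorly with the article's own account of that phase. The pilot label does not remove the problem, because effectiveness is a primary objective and the power is called adequate.

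**Conclusion.** The point holds as an unreconciled assumption and should be fixed. The power section and the Discussion give different expected effects for the same index, and the only power figure covers a change of 2 points per phase that continues after the intervention ends. It does not cover a small effect. Whether it roughly covers a medium one depends on the standardiser: 46% with an SD of 2, 86–93% with the implied total SD. All these figures are illustrations. They rest on the assumed 0.2 and 0.5 benchmarks, a two-sided test, and a residual SD back-solved from the 96% as a test of a 2-point contrast. The residual SD is left unprinted in a condensed article, and that is not itself the fault. It only limits how exactly the shortfall can be sized.

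**What to change.** 1. State one expected effect for the index, in points, in both the sample-size section and the Discussion.
2. Rerun the existing simulation with the residual SD and the tested contrast stated, over a range of smaller baseline-to-intervention changes (for example 0.4, 1.0, 1.5 and 2 points), with no further gain in follow-up.
3. Replace the 96% statement with that range and the smallest change detectable with 80% power. Alternatively, say that the study is powered only for a large change, and report objective 1.1.a as an estimate with a confidence interval.

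The cost is a rerun, some rewording and a less favourable stated figure. No participants, visits or measurements are added.

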##### Eating Behaviors

As shown in Figure 1, eating behaviors will be assessed daily for 15 weeks through a brief questionnaire: participants will have to report their food intake at the end of each day during the 2 weeks of the baseline period; then, every 3 weeks during the intervention period; and afterward, once per month during the follow-up period, representing a total of 105 potential measurement days per participant spread over a year (15 evaluation weeks × 7 measurement days).

A 12-item questionnaire will assess the consumption of specific food groups relevant to environmentally sustainable healthy diets as well as food waste (Table 2) [25]. The present food frequency questionnaire was designed considering the need to minimize the total number of items and make it suitable for daily assessment while adding items about relevant food groups to assess food environmental sustainability and healthiness. For each food group, the number of servings consumed during the day will be asked. Specific foods gathered in the assessed food groups will be detailed, and their serving sizes will be provided with examples that the participants can easily interpret. For instance, a serving of vegetable is reported as a medium size dish of mixed salad, cooked vegetables, or vegetable purée—1 big tomato, 2 carrots, and 1 glass of gazpacho (Figure 2). The size of a serving was established based on the Spanish Society of Community Nutrition recommendations and other Spanish documents [37,38]. The exception will be whole grains and virgin olive oil, which will be assessed in terms of their proportion among all the grains and added fats consumed during the day, respectively. The reason for assessing them as a proportion is because of the priority of healthy fat and carbohydrate intake rather than the total amount of fat and carbohydrate consumed, as the recommended amount of total added fats and carbohydrates depends on the specific energy needs of each person.

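### The 96% power is for a 2-unit rise per phase, not for the small to medium effect the article expects on the same index

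*Protocol article*

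**What the plan says.** The section on sample size and power says that recruitment is limited by resources and that power was simulated only for objective 1.1.a, the weekly diet index. Its result, "simulated power analysis indicated an adequate power value of 96"%, is obtained by "assuming an increase of 2 units in the environmentally sustainable healthy diet score per phase". In the recipe, "the intercept was set at 6", and the phase coefficient is minus 2 for the initial phase and plus "2 for the final phase based on our average expected change in the main outcome". The random effects are normal, "with SDs of 2 for the intercept and 0.5 for the slope", with correlation 0.2. A mixed model with phase as fixed effect was fitted 1000 times at the 0.05 level.

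The Discussion (Principal Findings) states the expectation for the same objective and the same index differently: a positive change "with small to medium effect sizes, as observed in most previous behavior change interventions".

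**The concern.** Both sections state the authors' own expectation for one outcome, and the two do not match in size. The power section builds in a change that is large on the only outcome SD the article gives, while the Discussion expects something small to medium. Power depends steeply on the assumed effect, so a figure computed at the larger change says little about the smaller one. Effectiveness is a primary objective, and this is the only power figure in the article. A reader who sees adequate power of 96% next to an expectation of small to medium effects would think the study is well placed to detect such effects. The same numbers would also carry over into the planning of the later randomized trial.

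**Working it through.** **Inputs from the article.** 21 participants and 15 weekly scores each ("up to 315 observations will be available in total (21 participants × 15 evaluation weeks"); phase means 6 - 2 = 4, 6, and 6 + 2 = 8; random intercept SD 2, random slope SD 0.5, correlation 0.2; alpha 0.05. The assessment schedule is 2 baseline weeks, "then, every 3 weeks during the intervention period; and afterward, once per month during the follow-up period". I split the 15 weeks as 2, 7 and 6.

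**Not printed, so assumed.** Residual SD, time unit of the random slope, tested contrast, two-sided test. Small to medium is read as 0.2 to 0.5 SD; the article gives no figure.

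**Step 1: size of the assumed effect.** Per phase: 2 / 2 = 1.0 SD. Baseline to follow-up: 4 / 2 = 2.0 SD. Small to medium on the same SD: 0.2 × 2 = 0.4 units to 0.5 × 2 = 1.0 unit. The assumed step is 2 to 5 times that range.

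**Step 2: can the 96% be reproduced?** Not strictly, because three inputs are missing. For intervention minus baseline at 2 units, the model-based (generalized least squares) standard error gives 96% with a residual SD of about 3.0 if the slope is per phase or over time rescaled to 0-1, and about 2.6 if it is per measurement occasion. At residual SD 2, power is 99.65% with a per-occasion slope.

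**Step 3: take the 96% at face value for a 2-unit contrast.**
- Implied SE = 2 / (1.96 + 1.75) = 0.539
- Power at 0.4 units: 0.4 / 0.539 = 0.74, about 12%
- Power at 0.6 units: 0.6 / 0.539 = 1.11, about 20%
- Power at 1.0 unit: 1.0 / 0.539 = 1.86, about 46%
- Detectable at 80% power: (1.96 + 0.84) × 0.539 = about 1.5 units

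**Step 4: assume a residual SD s instead.** With the slope per phase, the SE of intervention minus baseline is sqrt((0.25 + s²(1/2 + 1/7)) / 21).
- s = 1: sqrt(0.893 / 21) = 0.206; detectable 2.80 × 0.206 = 0.58 units
- s = 2: sqrt(2.821 / 21) = 0.367; detectable 2.80 × 0.367 = 1.03 units

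Across the three slope readings (per phase, per occasion, rescaled time):

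| Residual SD | Power at 0.4 units | Power at 1.0 unit | Detectable at 80% |
|---|---|---|---|
| 1 | 43-61% | over 99% | 0.5-0.6 units |
| 2 | 15-21% | 64-81% | 1.0-1.2 units |

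**Step 5: the scale limit.** At a follow-up mean of 8 and SD 2, the share of simulated participant means above 10 is P(Z > 1) = about 16%. With the slope per phase the SD there is sqrt(4 + 0.25 + 2 × 0.2 × 2 × 0.5) = 2.16 and the share is about 18%. The index cannot exceed 10.

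**The case against.** The article makes the 96% explicitly conditional on the 2-unit assumption, says the sample is limited by resources, and calls the study a pilot. It nowhere says that a null result would be read as no effect. All of that stands, and it is why the repair concerns the stated figure and not the sample size.

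The choice of SD also matters. If the residual SD really is near 3, the total SD is sqrt(4 + 9) = 3.61, and 2 units is d = 0.55, close to medium. Small to medium on that SD would have power of about 23-28% at d = 0.2 and 86-92% at d = 0.5. The per-phase mismatch then largely closes. However, the 4-unit total change is still d = 1.1, and a residual SD near 3 is hard to credit for a weekly average on a 0-10 scale. If the residual SD is near 1, a 1.0-unit effect is well powered, so it cannot be said that the whole expected range is underpowered.

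Two stronger readings are tempting, and the document supports neither.
- A reader might infer that the plan assumes a further rise after messages and feedback stop. The coefficients are phase averages. A score that climbs evenly from 4 to 8 during the intervention and then holds averages 4, 6 and 8 with no later gain. The Discussion expects linear improvement in some participants.
- A reader might infer that the 96% is arithmetically impossible. It is reachable with a large enough residual SD, and the residual SD, slope unit and tested contrast are not printed, so error is not shown.

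The absence of covariates and dropout from the simulation is detail that an article may leave to the full protocol, and I make nothing of it.

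**Conclusion.** The point holds as a conflict between the power section and the Discussion. The effect used for power is 1.0 SD per phase and 2.0 SD overall on the stated between-person SD, against an expectation of small to medium. Adequate power is therefore not shown for the expected effect. How far it falls short depends on the unstated residual SD and, to a lesser degree, the slope unit: from little or no shortfall at 1.0 unit with residual SD 1, to power of about 12% at 0.4 units if the 96% is taken as given for a 2-unit contrast. At 0.4 units, power is at most about 61% in every case examined. These figures rest on reading small to medium as 0.2 to 0.5 of the SD of 2, on the 2/7/6 split of weeks, and on complete data.

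**What to change.** Keep 21 participants. Reconcile the expected change in the power section with the one in the Discussion. Replace the single 96% with power, or the minimum detectable difference, for intervention minus baseline over about 0.4 to 1.0 units. State the residual SD, the time unit of the random slope and the contrast tested. Alongside the current scenario, run one with no gain from intervention to follow-up, and keep simulated scores within 0-10. The cost is a few hours of simulation and probably a less favourable stated figure; no extra participants or data are needed.

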#### Quantitative Data Analysis

Analyses for this project will be conducted with the statistical software R (R Foundation for Statistical Computing) [49]. The code and data generated for this study will be made open access when available.

##### Objective 1.1.a: Changes in the Environmental Sustainability and Healthiness of Diet

To test the main effect of the intervention on the environmental sustainability and healthiness of diet at the group level, linear mixed regression will be performed and expressed as measurement occasions (here, going from 1, first evaluation week, to 15, last evaluation week), using an ordered 3-categories phase variable as a fixed effect, which takes the values of baseline, intervention, and follow-up. Polynomial functions will also be fitted to the time variable to determine whether the index demonstrates any nonlinear patterns across time. If nonlinear patterns are detected, then other patterns (eg, quadratic, cubic, and piecewise) will be examined and selected based on visual inspections and goodness-of-fit indicators. Moderation analysis will be performed by exploring the role of the subjective socioeconomic level (ie, 3 socioeconomic groups entered as fixed effect) with regard to changes in diet. Fixed baseline characteristics will be included as control variables (ie, age, gender, education, income, and political orientation). Individual trajectories will be plotted, and heterogeneity in participants’ responses to the intervention will be discussed based on visual analyses using relevant guidelines for n-of-1 trials [50] (individual weekly changes in the whole diet will not be statistically modeled because only 15 observations will be available per participant).

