**Methods:**

We will run a series of ABA n-of-1 trials over a year, with the first A phase corresponding to a 2-week baseline evaluation, the B phase to a 22-week intervention, and the second A phase to a 24-week postintervention follow-up. We plan to enroll 21 participants from low, middle, and high socioeconomic statuses, with 7 from each socioeconomic group. The intervention will involve sending text messages and providing brief individualized web-based feedback sessions based on regular app-based assessments of eating behavior. The text messages will contain brief educational messages on human health and the environmental and socioeconomic effects of dietary choices; motivational messages to encourage the adoption of sustainable healthy diets by participants, providing tips to achieve their own behavioral goals; or links to recipes. Both quantitative and qualitative data will be collected. Quantitative data (eg, on eating behaviors and motivation) will be collected through self-reported questionnaires on several weekly bursts spread through the study. Qualitative data will be collected through 3 individual semistructured interviews before the intervention period, at the end of the intervention period, and at the end of the study. Analyses will be performed at both the individual and group levels depending on the outcome and objective.

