##### Objective 1.1.b: Changes in Individual Food Groups and Food Waste

An analytical strategy similar to that used for objective 1.1.a will be followed for testing the effect of the intervention on specific food groups, including red and processed meat, fruits and vegetables, ultraprocessed foods, and dairy products, and food waste. A linear mixed model similar to that performed for the first objective will be performed, but time will be expressed as measurement days instead of weeks, thus ranging from 1 to 105. In addition to the group and subgroup analyses performed for objective 1.1.a and maximizing the higher number of observations per participant within those outcomes, individual-level models will also be used to quantify the effect of the intervention on each participant separately from the others by following an idiographic approach.

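### The primary model uses an equally spaced occasion counter and a time form chosen from the data, and names no phase contrast as the intervention effect, so a gradual benefit can be lost from the phase coefficients

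*Protocol article*

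**What the plan says.** The section on objective 1.1.a describes a linear mixed regression whose time scale is "expressed as measurement occasions (here, going from 1, first evaluation week, to 15, last evaluation week". The intervention effect is to be tested in that regression "using an ordered 3-categories phase variable as a fixed effect, which takes the values of baseline, intervention, and follow-up". On the shape of change over time, the section adds: "Polynomial functions will also be fitted to the time variable to determine whether the index demonstrates any nonlinear patterns across time". If curvature appears, quadratic, cubic or piecewise forms are considered and "selected based on visual inspections and goodness-of-fit indicators". The section on objective 1.1.b carries the strategy over to the daily outcomes, where "time will be expressed as measurement days instead of weeks, thus ranging from 1 to 105".

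The Eating Behaviors section gives the real schedule: two baseline weeks, "then, every 3 weeks during the intervention period; and afterward, once per month during the follow-up period". The abstract gives the phase lengths: a 2-week baseline, "the B phase to a 22-week intervention, and the second A phase to a 24-week postintervention follow-up".

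The sample size section contains the only model written out in full. Phase is the sole fixed effect, and each participant has a random intercept and a random slope over time. The Principal Findings section expects straight-line gains as well as single-step changes in individuals.

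**The concern.** Three features act together.

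- **Time scale.** The counter treats gaps of 1, 3 and about 4 weeks as equal, which conflicts with the protocol's own schedule.
- **No fixed contrast.** No passage says which comparison of phases is the intervention effect, or whether time terms are in the model when it is read off.
- **Overlap of phase and time.** Phase is a step function of occasion. With time in the same model, a phase coefficient measures the jump at a phase boundary and no longer the difference between phase means. Twice-weekly messages over 22 weeks may well act gradually, and a gradual effect is what the time terms absorb.

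The size, and possibly the sign, of the main effectiveness estimate could then depend on a polynomial degree chosen after the data are seen. The same choice would carry into objective 1.1.b.

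**Working it through.** **Inputs from the article.** 15 evaluation weeks; spacing and phase lengths as above; 21 participants; random-effect SDs 2 (intercept) and 0.5 (slope), correlation 0.2; phase means 4, 6 and 8 in the power simulation.

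**Assumptions.** The timeline figure is not shown, so I take 2 + 7 + 6 = 15 evaluation weeks at weeks 1, 2 / 5, 8, ..., 23 / 28, 32, ..., 48. The residual SD is not stated, so a range is used. The random slope is taken on occasion.

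**The plan's own figure.** The stated 96% power cannot be reproduced without a residual SD. By generalised least squares (GLS), follow-up versus baseline has power 0.99, 0.96 and 0.93 at residual SD 3, 3.5 and 4. So 96% fits an SD of about 3.5. Adding occasion as a fixed effect lowers power at SD 3.5 to about 82%.

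**Time axis.** A constant 0.02 points per week becomes 0.02, 0.06 and 0.08 per occasion (0.02 × 1, 3, 4). For objective 1.1.b, the gap between the last day of one burst and the first day of the next is 21 - 6 = 15 days in the intervention and about 28 - 6 = 22 days in follow-up. The day counter codes each as 1.

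**Overlap.** With phase coded 1, 2, 3, its correlation with occasion is 0.91. Adding linear, quadratic or cubic occasion multiplies the variance of intervention minus baseline by 1.7, 2.8 or 5.5, and that of follow-up minus baseline by about 5 to 6.

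**A gradual effect.** Take an index of 4 at baseline, rising as 4 + 2 × (week - 2)/22 over the intervention, then held at 6. The mean intervention evaluation week is 14, so the intervention mean is 4 + 2 × 12/22 = 5.09. Noise-free least squares gives:

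| Model | Intervention - baseline | Follow-up - baseline |
|---|---|---|
| Phase only | +1.09 | +2.00 |
| Phase + occasion | +0.34 | +0.17 |
| Phase + quadratic occasion | -0.35 | -0.35 |
| Phase + cubic occasion | -0.01 | -0.21 |
| Phase + quadratic in weeks | -0.23 | -0.38 |

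The last row shows that calendar time corrects the axis but not the overlap. If the first intervention evaluation is in week 3 instead of week 5, the first three rows become +0.91/+2.00, +0.16/+0.17 and -0.53/-0.35.

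**An immediate step.** A step of +2 that is kept gives +2.00 and +2.00 in every model.

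**The model in the sample size section.** Here X holds phase only, and V = ZGZ' + σ²I, with Z = (1, occasion) and G having variances 4 and 0.25 and covariance 0.2 × 2 × 0.5 = 0.2. The estimate is (X'V⁻¹X)⁻¹X'V⁻¹y. For the same gradual effect:

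| Residual SD | Intervention - baseline | Follow-up - baseline |
|---|---|---|
| 1 | +0.40 | +0.32 |
| 2 | +0.54 | +0.65 |
| 3.5 | +0.73 | +1.12 |

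The differences in phase means are +1.09 and +2.00. A random slope with no fixed time term treats the average trend as a between-person deviation from zero and gives it little weight. With random phase effects instead, the fixed and random designs coincide, so with complete data GLS equals least squares and returns the phase means.

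**The case against.** **The joint model is not stated.** The article gives phase the task of testing the intervention and the polynomials that of detecting curvature. It never says that both sit in one formula, and the model written out has phase alone as fixed effect. This stands: the zero and negative estimates are conditional on the joint reading. Separate models do not remove the problem, because the written-out model shrinks the gradual effect too.

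**Adjusting for time has a purpose.** Without a control group, a rise that runs steadily through all three phases does not identify an intervention effect. A straight rise from 4 to 8 over the calendar gives +1.06 and +3.11 with phase only, and 0 and 0 with linear weeks added. Phase only credits that drift to the programme. This also stands: the choice is partly one of estimand, and it should be made before the data are seen.

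**Stronger readings that the article does not support.** A reader might infer that the ordered factor would miss an effect that reverses after the intervention. Ordered coding only reparameterises three means: for 4, 6, 4 the linear term is 0, but the quadratic term is (4 - 12 + 4)/√6 = -1.63, and nothing says that only the linear term is read. A reader might also infer that the unequal spacing alone will set off the nonlinearity check. At 0.02 points per week the largest departure from a straight line in occasion is 0.06 points on a 0-10 index, which would rarely be detected.

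**Conclusion.** The point holds in a conditional form. The equally spaced counter conflicts with the article's own measurement schedule in objectives 1.1.a and 1.1.b. The intervention contrast is not fixed before a data-driven choice of time form. If phase and time share a model, a gradual +2 effect can be estimated anywhere from +0.34 to -0.35 for intervention versus baseline, against a difference in phase means of +1.09. With phase fixed and a random time slope only, it comes out at +0.40 to +0.73 for residual SDs of 1 to 3.5. An immediate effect is not harmed.

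These sizes rest on the assumed 2 + 7 + 6 calendar, the assumed residual SDs and a ramp-shaped effect. The mechanism does not rest on the exact evaluation weeks: the alternative calendar gives the same pattern. It would be too strong to say that the plan will miss or reverse a true effect.

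**What to change.** 1. Use weeks or days since enrolment as the time variable in objectives 1.1.a and 1.1.b.
2. Name intervention versus baseline as the primary contrast and follow-up versus baseline as secondary. Estimate both from an unordered phase factor with a random intercept and random phase effect by participant, in place of a random time slope without a fixed time term.
3. Describe trajectories in a separate, pre-stated secondary model in calendar time: piecewise linear, with knots at the end of baseline and the end of the intervention.
4. Report a time-adjusted phase model as a sensitivity analysis.

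The cost is analysis wording, plus the calendar position of each assessment. The article does not say how response dates are recorded, so this should be confirmed. The price in interpretation is that the phase-only contrast includes any underlying drift and must be reported as change from baseline.
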